#### Exercise Group Class

An 8-week exercise program will be led by a registered kinesiologist and will follow the Fundamental Lifestyle Medicine group class session. The program will be structured yet adaptable to accommodate each participant’s abilities and limitations. Before the exercise program, the kinesiologist will present the Education Sessions-Fitness Fundamentals, where they will explain why participants should exercise and how to be safe doing so. A booklet describing all activities will be shared with the participants that outline safe exercise guidelines, the rating of the Borg care of perceived exertion [44,55], when to stop exercising (symptoms and what to do), how to adapt the program, and exercises plan with picture of each exercise. The kinesiologist will then teach the entire exercise program in group sessions with the participants. Each session will last 1 hour and will follow this sequence warm-up, resistance training, cardio, flexibility, balance, core, and cool down. The exercise will use body weight resistance and a physiotherapy band appropriate for each person’s capacity.

#### Enrollment

Participants will be screened according to the inclusion and exclusion criteria by the physician during their initial medical consultation. Eligible participants will be informed about the study’s purpose, procedures, potential risks, and benefits during the informed consent process before enrolment. Participants will be made aware of their right to withdraw consent at any point during the study without any impact on their care.

#### Retention

The research staff and health care providers will strive to build strong rapport with participants encouraging them to attend the 22 weekly classes held in person at the local Parry Sound Bobby Orr Community Centre. If participants are unable to attend in person, a web-based platform option will be provided, along with access to recorded sessions. This approach ensured accessibility and adaptability to meet diverse patient needs. Attrition will be closely monitored, and for those who choose to leave the study, a structured exit interview with a research assistant will be conducted to gather feedback and identify potential areas for improving the program.

### Ethical Considerations

This study received ethics approval from the Laurentian University Research Ethics Board (6021397) on July 6, 2023, and adheres to the guidelines stated in the Declaration of Helsinki. This study was registered at ClinicalTrials.gov (NCT06192251) in November 2023. Trained research staff informed participants of their right to withdraw themselves and the information collected on them up until the time of withdrawal, and informed consent was obtained. Patient data is available only to program health care providers and is segregated from research data. Participants are assigned a research code following the informed consent process, which links their research data through the study to allow appropriate analyses. Participant information is deidentified, and results will be published in this manner as well to ensure confidentiality.

## Results

The first cohort of participants was enrolled in late 2023 and is still under evaluation. Data collection for the second cohort began in mid-2024 and is currently underway, with a projected end date in early 2025. A total of 16 participants have been recruited as of November 2024. Data analysis will be conducted in mid-2025, and we anticipate submitting the final manuscript by the end of 2025. A mixed method analysis [42,43] will be used to analyze the quantitative and qualitative data, collected individually at enrollment, program completion (22 weeks), and follow-up (6 months after program completion). Focus groups will be conducted after the 22-week intervention to assess the program’s effectiveness and implementation.

Initial findings indicate that participants have gained knowledge about lifestyle changes, particularly in stress management and health behavior choices, and positively impacted their friends, family, and community by sharing their experiences. As more data is analyzed, it is anticipated that participants who commit to making changes will show improvement in their physical and mental well-being with the knowledge and practices learned from the classes and interdisciplinary health team.

In addition, initial participants included members of the local First Nation communities who raised concerns about accessibility for other First Nations such as challenges with significant travel and limited access to web-based platforms. In response to these concerns, there is confirmed interest in hosting a CLIP-ON cohort within these communities to ensure equitable access for all interested members.

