**Results:**

This study was approved by the Laurentian University Research Ethics Board (6021397) on July 6, 2023. The first cohort was enrolled in late 2023 and is still under evaluation. The second cohort began in mid-2024, and data collection is currently underway. A mixed methods analysis will be used at enrollment, program completion (22 weeks), and follow-up (6 months after program completion). Focus groups assessing the program’s effectiveness and implementation will take place after the 22-week intervention. Data will be analyzed in early 2025.

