**Figure 1 figure1:**
[figure not shown]
CLIP-ON protocol. The intake lifestyle and health progress questionnaire was inspired by the Lifestyle Assessment Short Form [46], the 36-Item Short Form Health Survey, and the Patient Health Questionnaire-9 [47,48]. The Physical Activity Readiness Questionnaire (PAR-Q+) [44] and PARmed-X [45] were used to measure physical activity readiness. The 6 pillars of health inspired by the American College of Lifestyle Medicine are nutrition, sleep, relationships, physical activity, risky substance use, and stress management [18]. Three- and 6-month health progress questionnaires were inspired by the questions used in the New York City Health [38,49,50], the Hospital lifestyle medicine program, and the Complete Health Improvement Program lifestyle medicine program at Vanderbilt University [51,52].

**Table 1 table1:** Participants and health care providers measurements.

Measurement	Time	Variables	Details
Intake Lifestyle and Health Participants Questionnaire	Baseline, 6 months, and 12 months	Food consumption, motivation and confidence, neighborhood food environment, physical activity, media use and screen time, substance use, sleep, health, behavior, and well-being, and socio-demographics	Administered through phone or online, inspired by inspired by the Lifestyle Assessment Short Form [46], the short form survey instrument SF-36^a^ and the PHQ-9^b^ [47,48].
Health progress questionnaire^c^	3 months and 6 months	Similar to the intake questionnaire but includes additional questions on social support, satisfaction with the program	Conducted by phone with a research assistant
Anthropometric measurements	Pre- and postprogram	Health, weight, BMI, and waist circumference	Measurements taken by health care providers
Hemodynamic measurements	Pre- and postprogram	Blood pressure and heart rate	Measurements taken by health care providers
Cardiometabolic measurements	Pre- and postprogram	Hemoglobin, ions (calcium, magnesium, phosphate, sodium, potassium), Fasting blood glucose, Glycated Hemoglobin, cholesterol Lipid panels (total cholesterol, high-density lipoprotein cholesterol, low-density lipoprotein cholesterol, plasma, triglycerides) creatine glomerular filtration rate, Urine test: microalbumin, and albumin-creatine ratio	Blood and urine tests collected for analysis
Health care provider questionnaire	Preprogram	Provider social demographics, credentials, practice location	Completed before program involvement

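### Cohort 2 data collection is projected to end in early 2025, before its follow-up 6 months after programme completion falls due, and the two stated analysis dates disagree

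*Protocol article*

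**What the plan says.** On cohort 2, the Results section says: "Data collection for the second cohort began in mid-2024 and is currently underway, with a projected end date in early 2025". The abstract agrees on the start: "The second cohort began in mid-2024, and data collection is currently underway".

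On the assessments, the Results section says that data are "collected individually at enrollment, program completion (22 weeks), and follow-up (6 months after program completion"). The abstract repeats the same three time points.

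On the analysis, the abstract says "Data will be analyzed in early 2025", while the Results section says "Data analysis will be conducted in mid-2025" and expects the final manuscript to be submitted by the end of 2025.

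Other sections time the follow-up differently. The Design section has telephone surveys at 3 and 6 months. Table 1 gives the intake questionnaire at "Baseline, 6 months, and 12 months", and the anthropometric, hemodynamic and cardiometabolic measures before and after the programme only. Future Directions lists an assessment at 12 months and beyond as a plan.

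On numbers, Limitations gives 8 participants in cohort 1, the Results section gives 16 recruited in total by November 2024, and the Design section anticipates 10% drop-out.

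**The concern.** A projected end of data collection should not come before the last scheduled assessment. Here the end date and the assessment schedule stand in the same paragraph and do not fit together. The abstract's analysis date has the same problem.

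What is at stake is the only assessment that the article places after the end of the programme in both the abstract and the Results section. The Strengths section presents the two-cohort design as a way to use cohort 1 feedback to improve the programme for cohort 2. If collection stopped on the stated date, cohort 2 would have no information on whether changes last 6 months beyond completion, and the number of people at that time point would halve. A follow-up window that has passed cannot be recovered.

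**Working it through.** **Inputs**
- Cohort 2 start: mid-2024 (abstract; Results). Assumed range: 1 May to 31 August 2024.
- Projected end of cohort 2 collection: early 2025 (Results). Assumed range: January to March 2025.
- Programme length 22 weeks; last assessment 6 months after completion (abstract; Results).
- Cohort 1 enrolled in late 2023 (Results). Assumed programme start: October 2023 to February 2024.
- Cohort 1 size 8 (Limitations); 16 recruited in total (Results); drop-out 10% (Design).

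**Step 1. Time from start to last assessment.** 22 × 7 / 30.44 = 5.06 months; 5.06 + 6 = 11.06 months.

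**Step 2. What early 2025 can correspond to.** Due date = start + 22 weeks, then + 6 months.

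| Cohort 2 start | 6 months from baseline | Programme completion | 6 months after completion | 12 months from baseline |
|---|---|---|---|---|
| 1 May 2024 | 1 Nov 2024 | 2 Oct 2024 | 2 Apr 2025 | 1 May 2025 |
| 1 Jun 2024 | 1 Dec 2024 | 2 Nov 2024 | 2 May 2025 | 1 Jun 2025 |
| 1 Jul 2024 | 1 Jan 2025 | 2 Dec 2024 | 2 Jun 2025 | 1 Jul 2025 |
| 1 Aug 2024 | 1 Feb 2025 | 2 Jan 2025 | 2 Jul 2025 | 1 Aug 2025 |
| 31 Aug 2024 | 28 Feb 2025 | 1 Feb 2025 | 1 Aug 2025 | 31 Aug 2025 |

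The stated end date is compatible with programme completion or with a survey 6 months from baseline. It cannot be reproduced from a follow-up 6 months after completion, nor from Table 1's 12-month questionnaire if that is counted from baseline. The initial visit precedes the sessions, so any gap between the two moves the post-completion date later.

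**Step 3. The reverse calculation.** Latest start = end date − 6 months − 22 weeks.
- End 31 January 2025: start by about 28 February 2024.
- End 31 March 2025: start by about 29 April 2024.
- End 30 April 2025: start by about 29 May 2024.

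The first two are not mid-2024. The conflict closes only in the third case, with a May 2024 start and early 2025 stretched through April.

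**Step 4. Cohort 1.** Starts from 1 October 2023 to 29 February 2024 reach the post-completion follow-up between 3 September 2024 and 1 February 2025. Cohort 1 can therefore be complete, or nearly so, by early 2025.

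**Step 5. Numbers at the post-completion time point.**
- Cohort 2: 16 − 8 = 8.
- Before drop-out: 16 with both cohorts, 8 with cohort 1 alone.
- After 10% drop-out: 16 × 0.9 = 14.4 (about 14) with both; 8 × 0.9 = 7.2 (about 7) with cohort 1 alone.

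**Step 6. Illustration of precision.** The article specifies no such analysis. For a mean change, with the 95% half-width taken as t(0.975, n − 1)/√n in SD units:
- Without drop-out: 2.131/√16 = 0.53 against 2.365/√8 = 0.84.
- With drop-out: 2.160/√14 = 0.58 against 2.447/√7 = 0.93.

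In either pair the interval is about 1.6 times as wide (0.84/0.53 = 1.58; 0.93/0.58 = 1.60).

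**The case against.** The strongest reply is that the end date may be right and the follow-up wording loose. Early 2025 suits a survey 6 months from baseline, and the article times its follow-up in several ways. This stands as a likely explanation, and it is why the anchor must be settled before any date is moved. It does not remove the conflict, because the abstract and the Results section both tie follow-up to programme completion.

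Second, the end date is a projection in a status report, not a data-lock rule. The mid-2025 analysis date would leave room for cohort 2 follow-up, for starts up to about 1 July 2024, if collection ran longer. This also stands. A reader might infer that the plan rests long-term follow-up on cohort 1 alone, or that cohort 2 follow-up cannot take place. The article says neither. The abstract's early-2025 analysis date, however, would leave no such room.

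Third, a reader might infer that RE-AIM Maintenance loses half its sample. How that dimension is measured is left to Multimedia Appendix 1, which is not shown, so the link is an assumption. The article is similarly silent on any mean change at that time point, and even 16 people give an imprecise estimate. Limitations already concedes the small sample.

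Fourth, the clinical measures are scheduled only before and after the programme. Enrolment, retention and focus groups do not depend on the late follow-up either. This stands and limits the scope.

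Finally, cohort 1 should not be described as having received a fixed, unrevised programme. The article also describes real-time improvements.

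**Conclusion.** The conflict is real. With mid-2024 read as May to August and early 2025 as January to March, every cohort 2 start date puts the follow-up after the projected end of collection. The analysis dates in the abstract and the Results section also contradict each other.

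The consequence is conditional. If the end date were applied as written, cohort 2 would contribute nothing 6 months after completion. About 7 people rather than about 14 would supply that time point after 10% drop-out (8 rather than 16 before it). This assumes that the 16 recruited by November 2024 are all the participants in the two cohorts. It reaches the questionnaire follow-up only and leaves the pre/post effectiveness comparison untouched. Any effect on the Maintenance dimension depends on the appendix.

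The correction is still worth making before data lock, because it decides whether anything can be said about lasting change in cohort 2.

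**What to change.** 1. Choose one anchor and set of time points for follow-up, and use it in the abstract, Design, Table 1, Results and Future Directions. State whether each of the 3-, 6- and 12-month assessments is counted from baseline or from programme completion, and whether the 12-month one belongs to this study or to later work.
2. If the last assessment is 6 months after completion, define the end of cohort 2 data collection as the last participant's final follow-up (about April to August 2025, depending on the actual start). Put data lock and analysis after it, and make the abstract's analysis date match the Results section.
3. If early 2025 must stand, state that post-programme follow-up comes from cohort 1 only, with 8 people or fewer, and make no claim of sustained effect for cohort 2.

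The cost is a few corrected dates and a delay of a few months to data lock. With the latest due date at about 1 August 2025, the end-2025 manuscript target can still be met.

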## Discussion

### Expected Outcomes

We anticipate that these findings will support the long-term goal of establishing a lifestyle medicine program for rural Ontario communities that combines education, digital platforms, and interactions with an interdisciplinary health team. Its holistic, patient-centered approach to medicine strives to promote lifestyle changes that can prevent and treat chronic diseases, transform patient care in a manner that has been demonstrated to be successful in large urban centers and encourage its adoption and adaptation by health care providers across Canada. Our long-term goal is to demonstrate that CLIP-ON positively impacts community health and decreases health care use by reducing the impact of chronic illness.

### Comparison to Previous Studies

CLIP-ON is the first lifestyle medicine program that will be conducted virtually and in-person in a rural Canadian community setting, while other Canadian lifestyle medicine interventions, such as Canadian Health Advanced Nutrition for Graded Exercise (CHANGE), have been implemented in large primary care settings in a physical format only [9,33]. This study will investigate the impact of incorporating all 6 pillars of lifestyle medicine as opposed to selected pillars [49-52,55-58]. It is also designed for patients with broad chronic diseases compared to other lifestyle medicine studies that focus on patients with specific chronic diseases [57,59-61]. Like the New York City lifestyle medicine program, CLIP-ON is built around all 6 pillars of health while providing individual support, goal setting, dietary recommendations, and monitoring support of an interdisciplinary health team [29,30,38]. However, Parry Sound’s catchment area spans 9222 km^2^ which is much larger than New York City’s 790-km^2^ urban setting [26,62]. The Parry Sound region includes 8 municipalities and townships and 4 First Nation communities housing over 42,000 residents who sometimes must travel long distances to access just primary care [26]. Therefore, understanding the unique challenges faced by rural Ontario communities will allow modifications to the program design that will be considerate of socioeconomic status, geographic and transportation barriers, preexisting patient-physician relationships, and cultural diversity.

The ability for participants to attend all programming virtually and in person was a core design to enhance program accessibility. This hybrid structure will also allow the onboarding of health care providers located throughout the province to engage in CLIP-ON more easily. Considering the vast catchment area of Parry Sound, limited transportation methods, and financial disparity within the region, it is understood that all participants may not have or have access to weekly transportation for classes. The research team will assist in identifying patient transport services to facilitate participant attendance at key program sessions wherever possible to enhance accessibility. A preexisting patient-physician relationship may result in discomfort for either participants or providers or introduce biased treatment towards some participants. Therefore, the research team will ensure that participants are matched with providers that they do not have an existing professional relationship with. Finally, special considerations will be incorporated for local Indigenous populations to be inclusive and respect their cultural requirements, including a land acknowledgment before every session and including providers with related experience and understanding of individual challenges and cultural differences.

These design elements distinctly position CLIP-ON as a whole health program designed to help all patients incorporate changes in various aspects of their lives in a setting where a lifestyle medicine program has yet to be introduced and piloted.

### Strengths

CLIP-ON is the first lifestyle medicine program designed for rural communities in Ontario. This included extensive engagement with local health care providers and community members to understand their unique challenges and preferences. It incorporates specific design elements such as virtual programming, which increases program accessibility for patients facing geographic barriers so that they can attend classes, exercise sessions, and meetings with health care providers remotely. The hybrid delivery model provides flexibility, allowing patients to choose in-person or virtual participation, which is crucial for geographically isolated individuals. In addition, it enables the recruitment of remote health care providers, increasing the feasibility of building an interdisciplinary health team for the program. This flexibility offers CLIP-ON to be a sustainable, impactful, and scalable model of preventative health care.

The involvement of an interdisciplinary team of health care professionals, including physicians, dietitians, health coaches, and kinesiologists, provides a comprehensive care approach that addresses various facets of participants’ health, enhancing the likelihood of sustainable health improvements. Furthermore, the program’s use of the RE-AIM framework ensures that implementation is evaluated through a robust and credible scientific approach, facilitating future scalability and applicability to other regions.

Initial observations have noted that the group structure and interactions during lifestyle medicine classes and exercise sessions facilitate social connectedness within the first cohort. The program’s focus on peer support and social interaction has led to increased participant accountability, as individuals share challenges and strategies within the group setting. Research shows that this peer support is often key to maintaining long-term behavior change [63]. Finally, the 2-cohort design of this study enables efficient incorporation of feedback from cohort one to enhance the program design for cohort two. The patient-centered approach, which integrates real-time feedback from participants and health care providers through focus groups and surveys, ensures continuous refinement of the program to meet participants’ needs and further enhance satisfaction and engagement.

### Limitations

This study has some limitations. Parry Sound’s small core town population of 6879 combined with the geographic barriers associated with its vast catchment area and lack of public transit limited the initial recruitment to only 8 participants in the first cohort, as opposed to the anticipated 10-12 [25]. This small sample size may limit the statistical power of the study, making it difficult to establish significant findings that are generalizable to other rural communities. To mitigate this, we are actively exploring strategies such as broader outreach to health care providers within the catchment area and forming partnerships with community organizations to raise awareness of the program.

Initial feedback also suggests that some participants found the program duration of 6 months to be too short for achieving and maintaining meaningful lifestyle changes. Extending the program duration could allow participants more time to solidify lifestyle adjustments. In addition, longer follow-ups will support the long-term impact of lifestyle medicine on chronic disease management. To facilitate this, additional follow-up sessions and group support beyond the 6-month mark are being established to reinforce lifestyle habits. This could offer a more gradual transition toward self-management for participants.

The web-based platform, while increasing accessibility for most, may present technological barriers for older participants or those unfamiliar with using web-based platforms. This could potentially reduce engagement for certain segments of the population, especially if support for technology use is not adequately provided. To alleviate this, we have introduced a brief training session for participants on how to use the virtual platform, and technical support is now available throughout the program.

